**Abstract:**

Multiple myeloma (MM) is a bone marrow neoplasia that causes bone pain in 70% patients. While preclinical models of MM have suggested that both nerve sprouting and nerve injury may be causative for the pain, there is a lack of clinical data. Thus, the primary aims of this clinical study are: (1) to provide a deep characterization of the subjective experience of pain and quality of life in MM patients; (2) to investigate disturbances in the bone innervation of MM patients. Secondary aims include exploring correlations between pain and serum inflammatory and bone turnover biomarkers. In a prospective, observational study (clinicaltrials.gov: NCT04273425), patients with suspected MM requiring a diagnostic iliac crest biopsy at Sheffield Teaching Hospital (UK) are invited to participate. Consenting patients answer seven standardized questionnaires assessing pain, quality of life and catastrophizing. Bone turnover biomarkers and inflammatory cytokines are measured in fasting serum samples, and bone innervation is evaluated in diagnostic biopsies. MM patients are invited to a follow-up upon completion of first line treatment. This will be the first deep characterization of pain in MM patients and its correlation with disturbances in bone innervation. Understanding how bone turnover and inflammation correlate to pain in MM is crucial to identify novel analgesic targets for this condition.

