## 2. Research Methods and Analyses

### 2.1. Study Design and Setting

A prospective, observational study in a cohort of patients undergoing a diagnostic bone marrow biopsy for suspected MM. This is a single-center study within an international collaboration; patients will be recruited and samples obtained at Sheffield Teaching Hospital NHS Foundation Trust, Sheffield, UK. Sample analyses will be performed at University of Copenhagen, Copenhagen, Denmark, or University of Southern Denmark, Odense, Denmark. The Danish Association for Multiple Myeloma was contacted during conceptualization; they confirmed the study’s relevance to MM patients. A flow diagram of the study design can be found in Figure 1.

The primary study aims are:To provide a deep characterization of the subjective experience of pain (including pain type, location and severity) and QoL in MM patients at diagnosis, compared to patients with a negative myeloma diagnosis (control group, presumably MGUS patients).To evaluate disturbances in bone innervation (presence, location and density of nerve fibers innervating the bone) in MM patients at diagnosis, compared to patients with a negative myeloma diagnosis.

Secondary aims of this study include evaluating the levels of bone turnover biomarkers and serum inflammatory cytokines in MM patients at diagnosis, compared to patients with a negative myeloma diagnosis.

Additionally, data on pain parameters and QoL, bone innervation and serum biomarkers from MM patients at diagnosis will be compared with data collected following first-line treatment. Correlations between pain and disturbances in bone innervation and serum biomarkers in MM patients before and after treatment will also be investigated.

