### 2.2. Study Population

All patients undergoing a diagnostic bone marrow biopsy for suspected MM between October 2019 and June 2021 will be invited to participate by their Hematology Consultant during their scheduled medical appointment. Inclusion and exclusion criteria are specified in Figure 2. Due to the impact of the COVID-19 pandemic on healthcare institutions, the study was paused between March 2020 and August 2020; thus, patient recruitment is expected to continue until June, 2021. The study population will comprise all consenting patients undergoing a diagnostic bone biopsy for suspected MM at Sheffield Teaching Hospital; data from patients with a negative MM diagnosis (confirmed MGUS or smoldering multiple myeloma, SMM, patients) will be used as control. Enrolled patients receiving a positive MM diagnosis will be invited to participate in a study follow-up, upon completion of first-line treatment (approximately 8 months after diagnosis). Patients may withdraw from the study at any point; collected data and tissue will be retained.

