### 2.4. Study Procedures

#### 2.4.1. Objectives 1 and 5: In-Depth Characterization of Pain in MM Patients

Patients who consent to participate will receive a booklet with a total of seven standardized questionnaires (Table 1), which will provide a deep characterization of their subjective experience of pain. Data from myeloma patients at diagnosis will be compared with that of patients receiving a negative myeloma diagnosis (control group). MM patients will be asked to complete the same set of questionnaires upon completion of first-line treatment; data from MM patients at diagnosis and following first-line treatment will be compared. The questionnaires include:BPI (Brief Pain Inventory, short version): two-factor questionnaire assessing the severity and interference of pain [15,16]. The severity component assesses location and severity of the pain, as well the analgesic relief provided by current therapy, if any. The interference component is composed by an affective and an activity subdimension. The BPI includes a Visual Analogue Scale (VAS) for assessment of pain intensity, which will be used to establish correlations between pain and disturbances in bone innervation, serum inflammatory and serum bone turnover biomarkers. Data from this questionnaire will allow to draw comparisons between pain severity and interference between MM patients and controls.FACT–BP (Functional Assessment of Cancer Therapy–Bone Pain): Initially developed for the assessment of pain in bone metastases, it measures bone pain and its effect on quality of life. This will provide information on whether myeloma patients suffer from bone pain, compared to controls. Moreover, this questionnaire is sensitive to clinical changes following therapy [17], and will provide important information on whether first-line anti-myeloma treatment improves bone pain and its effect on quality of life in myeloma patients.PCS (Pain Catastrophizing Scale): assessment of the extent of catastrophizing, which is subdivided in three domains: rumination, magnification and helplessness [18]. Mounting evidence suggests that catastrophizing (i.e., enhancing negative, anxiety-inducing thoughts) plays an important role in the subjective experience of pain; to our knowledge, this will be the first data on the role of catastrophizing in myeloma-induced bone pain.EORTC QLQ-C30 (European Organization for the Research and Treatment of Cancer Quality of Life Questionnaire-Core 30): assessment of quality of life in cancer patients. This questionnaire contains a measure of global health status, functional scales (including physical, role, emotional, cognitive and social functioning) and symptoms scales (including fatigue, nausea/vomiting, pain, dyspnea, insomnia, appetite loss, constipation, diarrhea and financial difficulties) [19]. As this questionnaire is widely used to assess the effect of cancer on QoL, it will allow to contextualize the effect of myeloma on QoL in comparison to other cancer types.EORTC MY20 (European Organization for the Research and Treatment of Cancer Quality of Life Questionnaire-myeloma module 20): Supplementary module to administer alongside the EORTC QLQ-C30 for the assessment of disease symptoms, side effects of treatment, future perspective and impact of disease on body image perception [20]. This questionnaire will allow comparisons to other cohorts of myeloma patients.EORTC CIPN (European Organization for the Research and Treatment of Cancer Quality of Life Questionnaire-chemotherapy-induced peripheral neuropathy module): assessment CIPN through a sensory, a motor and an autonomic scale [21]. Administration of this questionnaire at diagnosis will provide baseline data to compare the follow-up data to, allowing the identification of CIPN development after treatment.painDETECT: identification of a possible neuropathic component of pain [22]. This questionnaire, in combination with the EORTC CIPN, will allow the distinction between myeloma-induced neuropathy and chemotherapy-induced peripheral neuropathy”.

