## 3. Discussion

Pain is one of the most prevalent and feared cancer symptoms, and, together with fatigue, the main complain of MM patients [4,7]. The aim of this study is to provide a deep characterization of the subjective experience of pain, as perceived by MM patients, at time of diagnosis. Moreover, we will analyze the effect of first-line treatment on both pain and QoL.

Over the last few decades, methods to monitor symptoms and adverse effects, which ultimately contribute to the patients’ QoL, have gained attention. Traditionally, adverse effects are monitored by the clinicians following the Common Terminology Criteria for Adverse Events guidelines [25]. However, recent studies have shown that patient-reported outcomes (PRO) may be more accurate measures of patients´ symptoms, as clinicians often underestimate adverse effects [26]. This is also true in MM, as highlighted by a recent Danish study in which a poor correlation between PRO and clinician-reported adverse effects was found for all evaluated symptoms, including peripheral neuropathy, diarrhea, nausea and vomiting, fatigue, insomnia and appetite loss [27]. To overcome this, our study will apply a constellation of widely used, validated PROs to characterize myeloma-induced bone pain. These questionnaires include the short version of the BPI, which is the most commonly used tool for the evaluation of cancer pain [28] and assesses least, worst and average pain through numeric rating scales, which have been proved to have more power to detect differences in pain intensity than verbal categorical rating scales [29]. Additionally, the BPI evaluates the affective component of pain by assessing the relations with others, life enjoyment and mood, and the interference of pain with daily life, including walking, general activity and work. In combination with the FACT-BP, specifically developed for the assessment of bone pain, and the PCS, which focuses on catastrophizing and fear of pain, we expect to be able to capture relevant information on all pain dimensions (sensory, cognitive and affective) in myeloma patients.

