A common limitation of PRO to monitor HRQoL in longitudinal studies is the lack of compliance, which can compromise the power of clinical studies [33] and cofound the results (i.e., if the frailest patients do not complete PROs and drop out, the study results may overestimate QoL and underestimate toxicity and symptom burden). Recently, a Danish multicenter study evaluated, for the first time, a range of strategies to increase compliance to PRO in a population of myeloma patients [34]. In this study, myeloma patients at all disease stages were invited to participate by filling in PROs at 12 months intervals during a total of 24 months; the only exclusion criteria were set up as patients who do not speak Danish, or patients with a diagnosed psychiatric condition, so that the “real population” of myeloma patients in Denmark was represented. The results of this study showed that real-time monitoring of non-response patients, sending electronic reminders and educating study nurses leads to an increase of up to 95% PRO response rate, with frailty being a strong predictor for non-completion of self-administered questionnaires [34]. In an effort to improve compliance, patients recruited for this study will be given the option to fill in the questionnaire booklet themselves (self-reported PRO) while waiting for procedures in the hospital or take them home and return them in their next appointed visit. Follow-up calls will be placed to patients who fail to return the questionnaires within the agreed time-period. Thus, we expect compliance in this study to be high.

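### A one-group before-after comparison among patients who complete first-line treatment is presented as showing the effect of that treatment on pain and QoL

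*Protocol article*

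**What the plan says.** Section 2.1 calls the study "A prospective, observational study in a cohort of patients undergoing a diagnostic bone marrow biopsy for suspected MM". The Abstract states that "MM patients are invited to a follow-up upon completion of first line treatment". Section 2.2 is more specific: enrolled patients with a positive diagnosis "will be invited to participate in a study follow-up, upon completion of first-line treatment (approximately 8 months after diagnosis". Patients with a negative diagnosis (MGUS or smoldering MM) serve as controls at diagnosis, and the text gives them no second assessment. Figure 1, the flow diagram, could not be checked.

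The aims in section 2.1 and Objective 5 in section 2.3 are worded neutrally, and section 2.4.1 likewise says that "data from MM patients at diagnosis and following first-line treatment will be compared". Two other sentences go further:

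- Section 2.4.1, on FACT-BP: the questionnaire "will provide important information on whether first-line anti-myeloma treatment improves bone pain and its effect on quality of life in myeloma patients".
- Discussion, first paragraph: "Moreover, we will analyze the effect of first-line treatment on both pain and QoL".

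On loss of the frailest patients, the Discussion accepts that "the study results may overestimate QoL and underestimate toxicity and symptom burden". The limitations section covers consent of older and frailer patients, language, biopsy controls and biopsy site. It mentions neither the completer restriction nor the absence of a concurrent comparison.

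**The concern.** To say that treatment improves pain, one needs some idea of what pain would have done without it. Nothing in the described design supplies that. A change between diagnosis and roughly 8 months later could reflect treatment, the natural course of pain, altered analgesia (the BPI records relief from current therapy) or who is still being measured.

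The last of these follows from the invitation rule. Read literally, a patient who stops early or switches treatment does not reach completion and is not asked. The article's safeguards (choice of where to fill in the booklet, follow-up calls, structured interviews) help patients who have been invited. They do nothing for those who are not.

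At stake are Objective 5 and the post-treatment half of Objectives 6 to 8, which run in the same selected group. Section 2.4.1 also relies on follow-up to detect neuropathy that develops after treatment. A patient who stopped early because of neuropathy would be missed.

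**Working it through.** **1. The plan's own figure.** Section 2.4.5 uses a difference of 2.75 and an SD of 2.75, so the standardised difference is 1.0. With two-sided 5% (assumed, since the article states no alpha) and 80% power, the normal approximation gives 2 × (1.960 + 0.842)² / 1.0² = 15.7, so 16 per group. The two-sample t-test gives 16.7, so 17, with power 80.7% at 17. The stated 17 reproduces. It covers only the comparison at diagnosis. The article gives no figure for the before-after change, so there is none to reproduce.

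**2. What the before-after change contains.** Observed mean change in completers = treatment effect + change that would have occurred anyway + shift due to who is retained. The described data identify only the sum. The second term needs a comparison that is not there, and the third needs data on non-completers.

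**3. How large could the third term be?** The article gives no completion rate and no within-patient correlation, so this is an illustration only. Inputs:

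- SD 2.75 (section 2.4.5), assumed equal at both times; true mean change set to 0; scores treated as normal
- share not completing, d: 10% to 40% (assumed)
- correlation of non-completion with pain, c: 0.3 to 0.5 (assumed)
- within-patient correlation, ρ: 0.3 to 0.7 (assumed)

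Let λ = φ(z)/(1 − d), where z is the (1 − d) quantile of the standard normal. Then λ = 0.195 for d = 10%, 0.497 for 30% and 0.644 for 40%.

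*Non-completion linked to follow-up pain:* paired change = −SD × c × (1 − ρ) × λ.

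- Smallest: 2.75 × 0.3 × 0.3 × 0.195 = 0.05, so −0.05.
- Largest: 2.75 × 0.5 × 0.7 × 0.644 = 0.62, so −0.62 (simulation with 1,000,000 pairs: −0.61).

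*Non-completion linked only to pain at diagnosis (c = 0.5, d = 30%):* the sign reverses, paired change = +SD × c × (1 − ρ) × λ.

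- ρ = 0.3: 2.75 × 0.5 × 0.7 × 0.497 = +0.48.
- ρ = 0.7: 2.75 × 0.5 × 0.3 × 0.497 = +0.20 (simulation: +0.21).

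So with no true change, completers could show anything from about −0.6 to about +0.5 points, depending on a mechanism that the article cannot tell us.

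**4. Bias in the follow-up mean is a different quantity.** In the first scenario, the completers' follow-up mean compared with the baseline mean of all patients shifts by SD × c × λ: from 2.75 × 0.3 × 0.195 = 0.16 to 2.75 × 0.5 × 0.644 = 0.89 points too low. The paired change carries only the fraction (1 − ρ) of that.

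**5. Patients involved.** At least 35 participants, at least half with MM: 0.5 × 35 = 17.5, so 17 or 18. If 20% did not complete (assumed), that is 3 or 4 people.

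**The case against.** The formal objectives are neutral. They speak only of comparing the two time points, the study is openly observational, and no analysis or decision rule rests on the causal phrases. Elsewhere the article uses broader wording for the second time point (after first-line treatment, without *completion*). The follow-up biopsy is standard of care and serves to assess treatment efficacy, so poor responders are not excluded as such. How early stoppers are handled may be set out in the full protocol, and patients who have died cannot be asked under any design.

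Much of this stands. It limits the point to two sentences, one invitation rule and a gap in the limitations. It does not remove the point: both causal sentences are printed, and both places that define the follow-up invitation tie it to completion.

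Three stronger readings are tempting and not supported:

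- *The change is biased toward improvement.* A reader might infer this from the article's own warning about frail patients. Working step 3 shows that a paired change can shift either way.
- *Regression to the mean of a definite size.* The Introduction names pain as a main reason for consultation, so pain at diagnosis may be temporarily raised. But enrolment has no pain threshold, and the limitations section says patients enter with or without bone pain. A figure that assumes only patients above some baseline score does not describe this cohort.
- *Share lost times difference in score as the bias in change.* That product is the bias in the follow-up mean, not in the paired change.

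**Conclusion.** The point holds in limited form. A single-group before-after comparison among completers cannot show that first-line treatment improves bone pain, nor its effect on pain and QoL. The completer rule adds a risk of selection that the article recognises in principle but does not address for patients who are never invited. A neutral description of change would be sound.

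No size or direction can be given for the bias in the paired change. The range of about −0.6 to +0.5 points rests on assumed completion rates and correlations, and shows only that the sign is open. The conclusion also assumes that *completion* is meant literally and that the flow diagram shows no second assessment of a comparison group. The comparison at diagnosis and its sample size are unaffected. What changes is what Objective 5 and the follow-up part of Objectives 6 to 8 may conclude.

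**What to change.** 1. **Wording.** In section 2.4.1 (FACT-BP) and the first paragraph of the Discussion, replace *improves* and *effect of* by *change from diagnosis to after first-line treatment*.
2. **Limitations.** Add that follow-up is restricted to completers and that there is no concurrent comparison.
3. **Invitation rule, section 2.2.** Offer the follow-up booklet to every living MM participant when first-line treatment ends for any reason (completed, stopped early or switched), and record treatment status. If *completion* already meant this, one sentence should say so. Leave biopsies as in usual care.
4. **Reporting.** Give the number of MM patients without follow-up, the reasons, and their baseline pain. Show completers separately.

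The cost is wording, a few extra booklets, and a mixed treatment status that has to be flagged.

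Two further steps are not recommended. A booklet at a fixed 8 months for patients still on treatment would separate their pain scores from the post-treatment biopsy and serum needed for Objectives 6 to 8. Mailing the booklet to the MGUS and smoldering MM controls would not supply an untreated MM comparison.

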### Limitations of the Study

To date, data characterizing pain and QoL from the “real” MM population (patients who are not included in clinical studies are often older and frailer) or across different disease stages (i.e., before diagnosis, after first-line treatment) is scarce [32]. A possible bias of this study is that the older and frailer patients may not consent to participate; to reduce this bias, structured interviews will be offered to patients who feel too unwell to complete the study questionnaires on their own. Another possible bias is that, in this study, only English-speaking patients are asked to participate, as resources did not allow for translation of study documents to incorporate non-English speaking participants to give informed consent.

A major limitation of this study is the lack of appropriate bone biopsy controls. In this study, all patients undergoing diagnostic bone biopsies for suspected MM are invited to participate, thus including a subpopulation of confirmed MM patients and another with a negative diagnosis (confirmed MGUS or SMM patients, who will often present with elevated serum paraprotein but less than 10% malignant plasma cells in bone), who will serve as negative controls. However, it should be noted that biopsies from MGUS patients may also display bone or nerve disturbances, as they may also present low levels of abnormal clonal cells in the bone marrow. Obtaining bone biopsies from healthy volunteers could be considered, but due to the high invasiveness of the procedure, which often causes pain and discomfort for the patient, it was considered unattainable.

Another important limitation of the study is the area from which the biopsy will be extracted. Diagnostic trephine bone biopsies are generally extracted from the iliac crest, while MM patients may present bone pain, nerve disturbances or plasmacytomas in any other body area. Obtaining a pain-guided bone biopsy (i.e., a biopsy from the specific bone in which a patient describes a painful sensation) could be considered. However, all patients undergoing diagnostic bone biopsies at Sheffield Teaching Hospital will be included in this study, whether they present with bone pain or not, in an attempt to characterize pain in the entire MM population. Furthermore, collecting extra bone biopsies solely for research purposes would expectably decrease the number of consenting patients in the study. For that reason, only diagnostic biopsies will be evaluated and systemic bone innervation changes are expected to be observed. As hip is a common site of bone pain in MM [39], we expect to be able to identify nerve disturbances in the trephine bone biopsies collected for this study.

## 4. Ethics and Dissemination

This study is conducted in agreement with the Declaration of Helsinki and local laws and regulations. Eligible patients are informed about the study and given enough time to consider whether they want to participate. Written information is provided to all patients who may be interested in participating. Written informed consent is obtained by the research team.

Data will be analyzed with the appropriate statistical software and will be reported in compliance with the Strengthening the Reporting of Observational studies in Epidemiology (STROBE) guidelines [40], while inclusion of relevant items in the study protocol has been ensured following the Standard Protocol Items: Recommendations for Interventional Trials (SPIRIT) checklist [41] (Supplementary File S1).

Personal data will be handled confidentially. Patients will be initially approached by members of their standard health care team, and only after receiving explicit consent, research staff will approach them and invite them to participate in the study. Study participants will be assigned a unique personal study code. All research data, including the physical questionnaires’ booklets administered to the patients, will be pseudo-anonymized to this personal code. An Excel spreadsheet where the study code is linked to the patient´s hospital code (i.e., the decryption key) will be stored in a password-protected National Health Service computer and backed up on a secure, encrypted National Health Service share drive. All physical files containing personal data, such as consent sheets, will be stored in a secure location in a locked office, in a building protected by CCTV cameras and security guards. No identifiable data will be exported outside the United Kingdom, and patients will be explicitly consented to allow access to their personal data to research staff outside the medical team that is directly implicated in their standard of care.

The results of this study will be disseminated by publication in peer-reviewed scientific journals and participation in scientific conferences; authorship will be based upon the Vancouver recommendations. A layman summary of the study results will be administered to the study participants who consent to it.

